### 3.2. Participants’ recruitment and study design

#### 3.2.1. Participants

Study participants are recruited among stroke survivors admitted to a period of intensive neurorehabilitation treatment at the IRCCS San Camillo Hospital in Venice, Italy.

Inclusion criteria are: (1) age ≥18 years old; and (2) first ever cortical-subcortical, supratentorial ischemic or hemorrhagic, unilateral stroke, based on medical records.

Exclusion criteria are: (1) bilateral or pure cerebellar lesion; (2) presence of non-stabilized fractures; (3) diagnosis of other neurological and/or psychiatric disorder; (4) unstable medical condition (e.g., heart failure, untreated seizures, and psychiatric comorbidities); (5) any other relevant UL musculoskeletal impairment both before and after stroke, hampering assessment; and (6) inability to provide informed consent. Specific inclusion criteria for imaging analyses are (1) distinguishable lesion in FLAIR and (2) unilateral hemisphere lesion, while exclusion criteria are (1) bilateral lesion and (2) non-distinguishable lesion in FLAIR.

Specific exclusion criteria related to the instrumental technology (i.e., EEG, MRI, and TMS) employed in this project will be detailed in each specific section.

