#### 3.2.3. Study design

The study is a longitudinal cohort study. Every participant undergoes rehabilitation treatment according to the individualized plan agreed between the neurorehabilitation team and the same patient. Participation in the study does not result in the exclusion or reduction of ordinary treatment for the study-subjects. Full assessment is carried out before and after rehabilitation, according to the following scheme:

1.Initial assessment (T0): the participant undergoes clinical (motor and cognitive) assessments, blood sampling and instrumental investigations (i.e., imaging, neurophysiology, and electrophysiology), within 10 days from admission.2.Treatment during hospitalization: every participant undergoes a motor rehabilitation program consisting at minimum of 1 h/day of conventional therapy (CT) and one or more hours of other modalities such as technology devices (i.e., robotics and VR) for upper and lower limb or occupational therapy (OT) UL specific, according to the individual rehabilitation project agreed with the rehabilitation team (e.g., physiotherapist and medical doctor) and tailored on patients’ needs. Each session is adapted to the patient’s clinical condition and motor ability to perform exercises, accomplishing any harm that may occur (e.g., patients referring shoulder pain and high spasticity). Overall, rehabilitation treatment lasts at least 4 consecutive weeks, with an average duration of 8 weeks.3.Final assessment (T1): the participant undergoes the same clinical, biological, and instrumental investigations, as at T0, before discharge (approximately 8 weeks after admission).

A full description of the clinical (motor and cognitive) assessments, blood sampling procedures, rehabilitation treatments (CT and OT) and devices employed, and instrumental investigations carried out in this study will be described below. See Figure 1 for a schematic representation of time and procedures employed for this project.

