#### 3.2.4. Clinical motor profiling of recruited patients

Each participant recruited for the present study undergoes a detailed clinical assessment including: (1) collection of patient medical history and records; and (2) use of validated outcome measures for quantifying stroke severity, functional, and sensorimotor impairments.

The following outcome measures are used for quantifying the severity of stroke sequelae:

–National Institutes of Health Stroke Scale (NIHSS) (Page et al., 2012) is a 42-points scale for quantification of stroke severity.–Oxfordshire Community Stroke Project (OCSP) (Bamford et al., 1991) is a clinical classification system for ischemic stroke, allowing to predict the site involved by the brain infarct.–Functional Independence Measure (FIM) (Granger et al., 1986) is a 126-points scale for measuring the level of independence in activities of daily living (ADLs).

Following is the list of validated outcome measures for profiling UL sensorimotor impairments:

–Fugl-Meyer Assessment for Upper Extremity (FMA-UE) (Fugl-Meyer et al., 1975) is a 66-points scale for profiling UL impairment by quantifying performance of complex and segmental voluntary movements, grasping, and coordination. We will also the sensation and pain/range of motion domains of the FMA, with a total score obtainable of 0–24 and 0–48, respectively.–Action Research Arm Test (ARAT) (Carroll, 1965) is a 57-points ordinal scale quantifying hand and arm activities.–Medical Research Council (MRC) muscle strength scale (Compston, 2010) is a 5-points ordinal scale for assessment of voluntary force, applied to shoulder abduction (SA) and fingers extension (FE).–Reaching Performance Scale (RPS) (Levin et al., 2004) is a 36-points scale for assessment of voluntary UL reaching task.–Box and Blocks Test (BBT) (Mathiowetz et al., 1985a) is a 1-min test for assessment of gross manual dexterity.–Nine Hole Pegboard Test (NHPT) (Mathiowetz et al., 1985b) is a 50-s test for assessment of fine finger dexterity.–Trunk Control Test (TCT) (Collin and Wade, 1990) is a 100-points outcome measure for assessment of trunk control.–Modified Ashworth Scale (MAS) (Bohannon and Smith, 1987) is an ordinal scale for assessment of muscle spasticity.

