### 3.5. Statistical modeling

Statistical methods will be based on the intention-to-treat principle (McCoy, 2017). Given the heterogeneity of the measures collected, data will be normalized before being analyzed and in case of high percentages of missing data, they will be subjected to multivariate imputation (Sterne et al., 2009). The statistical analysis will be as follow:

–Descriptive statistics (median, interquartile range, mean, standard deviation, and absolute and percentage frequencies) will be applied to describe the sample characteristics and data.–Data distribution, assessed with the Shapiro–Wilk test, and appropriate correlation tests (i.e., Spearman’s rho, Pearson’s *r*, Cramér’s V, or point-biserial correlation coefficient) will be performed to study the presence of associations between the variables (collinearity).–Data grouping. Patients will be divided in two categories (i.e., *Responders* and *Non-Responders*) according to responsiveness to therapy, defined as an improvement of 5 points relative to the minimally clinically important difference (MCID) of the primary outcome measure (i.e., FMA-UE) (Page et al., 2012). To assess whether there is a statistically significant difference in the dose of therapy between the Responder and Non-Responder patient groups, Student’s *t*-test for unpaired data or Mann–Whitney test for each clinical variable will be performed, depending on distribution properties, as already proposed in previous studies (Salvalaggio et al., 2023). Then, with the aim to identifying the best set of variables (regressors) that can predict UL motor recovery in patients, appropriate regression models will be estimated. This step will be preceded by the evaluation of the requirements of the chosen model and by considering possible adjustments for mediating, moderating, and confounding factors. Prior to model fitting, preliminary diagnostic check will be made [i.e., variance inflation factor (VIF) for the study of collinearity independence among predictors]. Selection of the best set of regressors will be made taking into account appropriate indices. A diagnostic analysis (goodness-of-fit) of the model will be performed on the model to verify its assumptions and the fit to the available data. The statistical significance level will be set at *p* < 0.05, and all statistical analyses will be performed using the latest version of R software (R Core Team, 2022).

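### With a 66-point cap, a 5-point responder rule and no entry criterion for arm impairment, patients starting at FMA-UE 62-66 are Non-Responders by arithmetic

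*Protocol article*

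**What the plan says.** Four statements in the protocol article bear on this.

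- **Who enters (3.2.1).** "Study participants are recruited among stroke survivors admitted to a period of intensive neurorehabilitation treatment". The inclusion list has two items: "Inclusion criteria are: (1) age ≥18 years old; and (2) first ever cortical-subcortical, supratentorial ischemic or hemorrhagic, unilateral stroke, based on medical records". Of the six exclusions, the only one naming the arm is "any other relevant UL musculoskeletal impairment both before and after stroke, hampering assessment". It removes musculoskeletal problems. It does not remove a normal or nearly normal arm.
- **What they receive (3.2.3).** Conventional therapy plus "one or more hours of other modalities such as technology devices (i.e., robotics and VR) for upper and lower limb", or upper-limb occupational therapy, under an individual plan. Admission for a mainly lower-limb problem is therefore compatible with entry.
- **The scale (3.2.4).** The FMA-UE "is a 66-points scale for profiling UL impairment".
- **The rule (3.5).** Responsiveness is "defined as an improvement of 5 points relative to the minimally clinically important difference (MCID) of the primary outcome measure (i.e., FMA-UE". No exception is made for high baselines. Dose of therapy is then compared between the two groups by t-test or Mann-Whitney test. Regression models of upper-limb recovery follow, and their outcome variable is not named.

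Section 4 describes Responders a little differently, as patients who go beyond the MCID. That could mean strictly more than 5 points.

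**The concern.** The rule is meant to separate patients who responded to therapy from those who did not. For a patient near the top of the scale it measures only the room left to improve. The Non-Responder group can then hold two opposite kinds of patient: those with almost no deficit, and those with a deficit that did not change.

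Two uses of the grouping are exposed.

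1. **The dose comparison**, which section 3.5 ties directly to the grouping. If near-normal arms receive a different number of upper-limb hours from other arms, their forced placement among Non-Responders shifts that group's mean dose for a reason unrelated to response.
2. **Any model that takes responder status as its outcome.** Section 1 lists preserved motor evoked potentials, preserved fractional anisotropy and strong shoulder abduction and finger extension as candidate favourable predictors. Patients starting at 62-66 are the ones expected to have these features, yet none can count as a responder. Section 2 makes identifying the best responders part of the overarching objective.

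**Working it through.** **Plan's own figure.** The article gives no figure for baseline scores or for the responder rate, so there is none to reproduce here. The 54 evaluable patients of section 3.2.2 do reproduce (paired comparison, d = 0.45, two-sided α = 0.05: power 0.901 at n = 54 and 0.895 at n = 53). That calculation concerns the mean pre-post change and does not use the responder split.

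**Step 1: who cannot respond.** Largest possible gain = 66 − T0.

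| T0 FMA-UE | Largest gain | Gain ≥ 5 possible? | Gain > 5 possible? |
|---|---|---|---|
| 60 | 6 | yes | yes |
| 61 | 5 | yes, only with a perfect T1 score | no |
| 62 | 4 | no | no |
| 63 | 3 | no | no |
| 64 | 2 | no | no |
| 65 | 1 | no | no |
| 66 | 0 | no | no |

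The impossible range is 62-66 for a gain of at least 5, and 61-66 if section 4 means more than 5. If section 3.5 were read literally as 5 points beyond the MCID, the range would be wider still.

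**Step 2: how many (assumed).** Let c be the share starting at 62-66. The article does not give c.
- c = 5%: 75 × 0.05 = 3.75, about 4 patients
- c = 10%: 75 × 0.10 = 7.5, about 8
- c = 20%: 75 × 0.20 = 15

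**Step 3: share of the Non-Responder group (assumed).** Let p be the response rate among patients who can respond, taken as 40% to 60%. The forced share is w = c / [1 − (1 − c)p].
- c = 5%: 0.05/0.62 = 8% to 0.05/0.43 = 12%
- c = 10%: 0.10/0.64 = 16% to 0.10/0.46 = 22%
- c = 20%: 0.20/0.68 = 29% to 0.20/0.52 = 38%

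**Step 4: effect on the dose comparison.** If ceiling patients differ from the other Non-Responders by D hours on average, the Non-Responder mean moves by w × D. With w between 0.08 and 0.38, each hour of difference moves the mean by 0.08 to 0.38 hours. The article gives neither the size nor the sign of D.

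**Step 5: effect on a marker, only if responder status is the outcome (all inputs assumed).** Below the ceiling, half the patients have a favourable marker, and response is 75% with it and 45% without. All ceiling patients have it. The odds ratio below the ceiling is (0.75/0.25)/(0.45/0.55) = 3.67. Adding the ceiling patients gives

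OR = [0.375(1 − c) / (0.125(1 − c) + c)] / (0.45/0.55).

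- c = 5%: (0.356/0.169)/0.818 = 2.6
- c = 10%: (0.3375/0.2125)/0.818 = 1.9
- c = 20%: (0.300/0.300)/0.818 = 1.2

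Under these inputs the association is weakened throughout the 5-20% range and does not reverse.

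**The case against.** The strongest reply is that the problem may be nearly empty. These are inpatients in intensive neurorehabilitation who stay about 8 weeks on average; the study's title concerns upper-limb impairment; and the wording of the musculoskeletal exclusion suggests that a stroke-related arm deficit is taken for granted. The share at 62-66 could be close to zero. This stands as a limit on size. It does not cure the rule, because none of it is an entry criterion.

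A reader might infer that favourable markers will be turned into markers of non-response. The documents do not support that. Section 3.5 does not name the regression outcome; if it is a score, the forced labels do not enter those models. Even with responder status as outcome, the illustration shows weakening and no reversal over the assumed range.

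A reader might also infer that the dose comparison is biased because mild patients receive fewer upper-limb hours. The article says only that treatment is individualised and gives no hours by severity. Distortion is possible but not shown.

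Section 3.5 allows for adjustment for confounders. That leaves room for baseline FMA-UE without naming it, and adjustment does not make a response possible for patients who cannot reach the threshold. The comparison of dose is in any case an unadjusted two-group test.

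Analysis populations are often left to a fuller plan. The point here is narrower: the responder rule and the entry criteria are both stated, and together they give some patients a wrong label.

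**Conclusion.** The point holds as a defect in a stated rule. As published, T0 scores of 62-66 (61-66 under the stricter wording of section 4) cannot lead to Responder status, and these patients enter the dose comparison as Non-Responders. That part rests only on the 66-point maximum, the 5-point threshold and the entry criteria.

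Its practical size is unknown. If 5-20% of patients start in that range and 40-60% of the others respond, about 4-15 of 75 patients are mislabelled and they make up roughly 8-38% of Non-Responders. Both percentages are assumptions. The effect on predictor models depends further on an outcome choice the article leaves open.

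A reader might conclude that the eligibility criteria must be tightened. That does not follow. Data collection began in August 2021, recruitment was planned as consecutive, and a mid-study limit would change the cohort. The fault can be dealt with in the analysis, using data already collected.

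**What to change.** 1. State the rule once, in sections 3.5 and 4 alike: a Responder has T1 minus T0 FMA-UE of at least 5 points.
2. Restrict the Responder/Non-Responder classification, and every analysis that uses it (including the dose comparison), to patients with T0 FMA-UE of 61 or less. Report how many patients were above 61.
3. Alongside it, in all patients, analyse T1 FMA-UE with T0 FMA-UE as a covariate. Note that the scale ceiling still limits T1, so this analysis reduces the problem without removing it.

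No new data and no eligibility change are needed; the cost is a few sentences in the analysis section. The downside is a smaller responder analysis. Under the assumed 5-20% it would lose about 4-15 of 75 patients, leaving about 71 to 60. The cut at 61 removes only those for whom response is impossible: a patient at 60 or 61 still needs a T1 score of at least 65 or 66, and the report should say so.

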#### 3.2.2. Sample size calculation

The sample size was calculated with regard to the main motor outcome assessing UL function (Fugl-Meyer Assessment for Upper Extremity – FMA-UE). From published data on the same cohort study design of stroke survivors admitted at the IRCCS San Camillo Hospital (Salvalaggio et al., 2023), and undergoing the same rehabilitative treatments described in this protocol, is expected that UL function improves with moderate standardized effect (Cohen’s *d* = 0.45), according to FMA-UE. Assuming an equivalent effect size *f* = 0.225, for repeated measures, within factors multivariate analysis of variance (MANOVA) design (Chen and Chen, 2010), in one group with two measurements correlating 0.5, given α = 0.05 and 1-β = 0.90, a total recruitment of 54 consecutive subjects would be needed. Considering a drop-out rate of 40%, a final number of 75 patients will be considered sufficient to conclude the study.

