*(A) T1-weighted*: this sequence is primarily used to study gray matter (GM) structural macroscopic tissue in both cortical and subcortical brain regions. GM changes have been widely reported in stroke patients (Diao et al., 2017) and associated with motor recovery (Abela et al., 2015). Brain tissues can be segmented into total GM, WM and cerebrospinal fluid (CSF), and cortical and subcortical regions. Brain tissues and (sub)-cortical regions will be visually inspected to ensure an accurate segmentation. T1-weighted images will also be used to carry out the lesion segmentation procedure (i.e., the reconstruction of individual patient’s lesion subsequent the stroke event). The identification of 3D lesion maps for all the recruited patients is a necessary step for subsequent processing and analysis not only of the acquired MRI data, but also for the neurophysiological data.

*(B) Diffusion MRI (dMRI)*: diffusion MRI exploits the principles of traditional MRI to measure the random motion of water molecules and subsequently to (I) infer information about WM microstructural properties and (II) delineate the gross axonal organization of the brain (Bammer, 2003). As dMRI is particularly sensitive to susceptibility-induced distortions, here we have adopted a correction strategy based on the complementary information from pairs of diffusion images acquired with reversed phase-encoding (PE) directions to correct for distortions. Moreover, a multi-shell acquisition was specifically implemented for this project, which will allow to account for crossing fibers issues and will provide a higher resolution for the intravoxel structure. These aspects are crucial when attempting to accurately reconstruct WM bundles in the presence of lesions and assess how micro-structural connectivity can be affected by stroke and modulated by rehabilitation (Konieczny et al., 2021). FA, mean diffusivity (MD), axial diffusivity (AD), and radial diffusivity (RD) maps, known to be sensitive to brain insults, such as stroke, can be generated. Individual matrices reflecting structural connectivity will be derived and used as predictors of motor recovery (Rocha et al., 2022).

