## 4. Discussion and summary

The identification of sensitive measures, which allows a deep investigation of neural processes underpinning recovery after focal injury, is a current need, particularly in clinical settings (Bernhardt et al., 2016; Hayward et al., 2017).

The study described here will generate a rich multi-modal and integrated dataset in stroke patients, characterized by a wide range of complex measures derived from traditional and advanced assessment modalities. This is an essential step both to confirm acknowledged predictive models and to develop new ones for a careful evaluation of UL functional recovery following rehabilitation. The identification of a set of markers, able to finely predict the UL rehabilitation induced sensorimotor recovery after stroke, could be particularly useful for patients’ stratification (e.g., *Responders* and *Non-Responders*, according to patients who overcome the MCID in clinical scales) (Dimyan et al., 2022). This will contribute to steer the actual rehabilitation practice toward a more personalized treatment (or combination of treatments), and therefore reach the best possible outcome at a functional and sensorimotor level.

This study is not without limitations and challenges. Indeed, the use of numerous outcome measures and evaluation methods employed here require a careful statistical planning and modeling, also considering the potential of missing data. Moreover, the lack of a control cohort may limit the generalizability of “candidate” prognostic factors in terms of causal relationship between predictors and final outcomes (Kent et al., 2020). For this reason, we envisage, as a possible extension of the present study, the external validation of the identified model(s) using a randomized controlled trial (RCT) or a cost-effectiveness study, which will eventually provide the possibility to guide the process of clinical decision-making regarding the time of intervention, promoting the greatest chance of recovery of the compromised functions.

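### The set of predictors is selected from a pool that is large for the sample, and the only check described is fit to the same data, so apparent performance will be optimistic

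*Protocol article*

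**What the plan says.** Section 2 sets the overarching objective as a set of variables, from many assessment modalities, that reliably predicts upper-limb motor recovery. The abstract treats the measures derived from all acquired data as candidate predictors. On diffusion MRI, Section 3.4.3 says: "Individual matrices reflecting structural connectivity will be derived and used as predictors of motor recovery". Functional connectivity matrices are also derived. Section 3.4 says that physiological and imaging data will be turned into interpretable features for the models, without giving their number or the method.

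Section 3.5 describes the modelling. After a collinearity check by variance inflation factor (VIF), "Selection of the best set of regressors will be made taking into account appropriate indices". Then: "A diagnostic analysis (goodness-of-fit) of the model will be performed on the model to verify its assumptions and the fit to the available data". The significance level is 0.05. Section 4 mentions "as a possible extension of the present study, the external validation of the identified model(s", by means of a randomized trial or a cost-effectiveness study. Section 3 cites TRIPOD for reporting.

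Section 3.2.2 sizes the study for the pre-post change in FMA-UE: "a total recruitment of 54 consecutive subjects would be needed", and with 40% drop-out "a final number of 75 patients will be considered sufficient to conclude the study". The article gives no sample-size reasoning for the prediction model and no count of candidates.

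**The concern.** If variables are chosen because they fit a given set of patients, fit in those patients no longer measures prediction. The selection has already used up chance associations, and the larger the pool relative to the sample, the more of these there are to use. Goodness-of-fit examines assumptions and fit in the development data, and VIF looks only at the predictors. Neither can tell a model that predicts from one that has absorbed noise.

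The sequence in Section 3.5 ends at that point, and the only validation named lies outside the study. Carried out as written, it can produce a selected set with respectable R² or AUC and a significant overall test although nothing predicts recovery. Section 4 intends the result to support stratification into responders and non-responders and to steer practice towards personalized treatment, so the main objective is at stake.

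**Working it through.** **1. Sample size.** Section 3.2.2 gives f = 0.225 (d = 0.45), two measurements correlating 0.5, α = 0.05 and power 0.90. The one-group repeated-measures F test is equivalent to a paired t test with d = 0.45, and n = 54 gives power 0.901. The plan's figure of 54 reproduces, but for a mean change and not for a prediction model. The enrolment of 75 matches 54 × 1.4 = 75.6. Losing 40% of 75 leaves 75 × 0.6 = 45. The number of completers is therefore 45 on the plan's own drop-out rate and 54 on its target. If missing data are imputed, the analysis could include up to 75.

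**2. Candidates.** My count of named measures, one score per test, from Sections 3.2.4 to 3.2.9, 3.4.1 and 3.4.2:

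| Group | All named | Scheduled for all patients |
|---|---|---|
| Severity and motor scales | 14 | 14 |
| Drug classes | 5 | 5 |
| Frailty | 1 | 1 |
| Dose codes (number of devices; three hour totals) | 4 | 4 |
| Neuropsychological tests | 22 | 8 |
| miR-941 | 1 | 1 |
| EEG | 6 | 6 |
| TMS (four measures, two hemispheres) | 8 | 8 |
| **Total before MRI** | **61** | **47** |

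The neuropsychological row is 6 core + 11 right-stroke + 7 left-stroke − 2 shared = 22. Those given to every patient are 6 + 2 = 8, so 14 are specific to lesion side. The totals are approximate. TMS, for example, has its own exclusion criteria.

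MRI adds tissue and diffusion measures and the matrices. A symmetric matrix of R regions has R(R − 1)/2 entries, which is 78 at R = 13, already above 75. The article does not give R or say that entries are used one by one.

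**3. Null simulation.** Section 3.5 leaves the selection method open, so the following are assumptions: independent normal candidates unrelated to the outcome, forward selection by AIC or BIC, and at most 10 terms. Mean results:

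| Patients | Candidates | Apparent R², AIC / BIC | R² in new patients, AIC / BIC |
|---|---|---|---|
| 75 | 47 | 0.39 / 0.16 | −0.55 / −0.20 |
| 54 | 60 | 0.59 / 0.39 | −1.00 / −0.59 |

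Between repeat runs the apparent figures move by about 0.02 and the new-patient figures by up to about 0.1.

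**4. Sensitivity.**
- *Correlated candidates (assumed correlation 0.5).* Apparent R² (AIC / BIC) is 0.35 / 0.13 at n = 75 with 47 candidates, and 0.58 / 0.27 at n = 54 with 60. R² in new patients stays negative.
- *Discrimination.* With 50 candidates and n = 75, three selection rules (p < 0.05, BIC, best five) give apparent AUC 0.67 to 0.74 against 0.50 in new patients.
- *A much smaller pool.* With 20 candidates and n = 75, apparent R² is 0.06 to 0.19, and the overall model is significant at 0.05 in 53% to 78% of null runs.

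**The case against.** The strongest reply is that this is a condensed article and Section 3.5 fixes very little. The model and the selection index are left open, and a fuller analysis plan might specify penalization or resampling. Goodness-of-fit is called a diagnostic analysis and is not declared to be the performance estimate. TRIPOD is cited, and Section 4 recognizes that so many measures need careful planning and calls the factors candidates. Forward selection is my assumption. With imputation, n = 75 is a plausible analysis size, and there the optimism is smaller.

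Most of that stands as a limit on size. It does not remove the point. The article goes beyond silence: it sets out select, then check fit to the available data, and assigns validation to a possible other study. A good selection index would still leave same-data fit as the only check described. TRIPOD is invoked for reporting, and no validation step accompanies it.

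Three stronger readings are tempting, and the documents do not support them:
- *Candidates certainly outnumber patients.* The 47 scores scheduled for everyone are below 54 and 75, and even 61 is below 75. The claim would need matrices entered entry by entry, or heavy drop-out, and Section 3.4 allows reduction to features.
- *Univariate tests at 0.05 screen the predictors.* The group tests are said to run "for each clinical variable will be performed, depending on distribution properties", which is unclear wording, but their stated purpose is to compare dose of therapy between responders and non-responders.
- *VIF cannot be computed.* Section 3.5 applies it among predictors before fitting and does not say that it is run on the whole pool.

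**Conclusion.** The point holds in this form: selection from a pool that is large for the sample, with goodness-of-fit to the same patients as the only check described, cannot show that the chosen variables predict recovery. It does not depend on having more candidates than patients.

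On the more favourable reading (75 patients, 47 candidates), pure noise yields an apparent R² of about 0.16 to 0.39. With 54 patients and 60 candidates it yields about 0.39 to 0.59. R² in new patients is below zero in every setting. These figures rest on my count of candidates, an assumed forward selection capped at 10 terms, and independent candidates. Correlation lowers the apparent figures somewhat. The true size depends on the method finally used and on how far imaging data are reduced. Because the main objective is affected and the remedy needs no new patients or measurements, it should be settled before the models are fitted.

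**What to change.** Amend Section 3.5, or fix in the analysis plan before modelling, as follows:

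1. Limit candidates to T0 measures plus dose of therapy. Either draw them from a short prespecified list, with connectivity reduced to a few prespecified summaries, or fit a penalized regression such as ridge or elastic net.
2. Repeat every data-driven step (normalization, imputation, selection, tuning) inside each bootstrap resample or each fold of a nested cross-validation.
3. Report optimism-corrected R² or AUC and calibration slope as the main performance result.
4. Keep goodness-of-fit as a model diagnostic only.

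The external study envisaged in Section 4 remains useful but does not replace these steps. The cost is some wording and computing time, lower reported performance and shrunken coefficients.
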